### Data analysis

Across 2400 EMR pulls, 720, 480, and 1200 are expected to occur during Usual Care, Preparation/Implementation, and Sustainment phases, respectively. Preliminary analysis will include bivariate and multivariate analysis using correlations, cross-tabulations and regression models to ascertain data structure, statistical distribution, and study artefacts. Analyses for all Aims will be performed using multilevel structural equation models (MSEM) in Mplus 8.10 [51]. We conducted Monte Carlo simulation power analyses modeling treatment effects and outcome variance nested in OTPs (anticipated ICC: 15%) and/or counselors (anticipated ICC: 10%; see Table 2). There is no expected missing data from EMR pulls, although at OTP and counselor levels, analyses will follow an intent-to-treat approach to dealing with missing data. Across all analyses, we will employ a moderator-first approach to the equity of treatment effects to ensure that group-level differences can be validly interpreted and that we are sensitive to differential treatment effects among patient subgroups. Similarly, we will examine whether significant variance in treatment effects occurs at counselor- or OTP-levels (through exploring the size of random effects variance parameters) before concluding whether treatment effects can be validly interpreted as fixed at the patient-level.

**Table 2 Tab2:** Results of Monte Carlo simulation analyses examining power to detect aim 1 and aim 2 outcome effects

Outcome	Comparison (*n* per condition)	Predicted rates/effects	Power at α = .05
*Aim 1*			
Reach^a^	Usual care (720)–preparation/implementation (480)	2–22%	98%
Adoption^b^	Usual care (70)–preparation/implementation (70)	10–50%	95%
Implementation	No comparison		
Maintenance	Preparation/implementation (480)–sustainment (1200)		
*Aim 2*			
Stimulant abstinence	Usual care (720)–preparation/implementation (480)	25–40%	90%
Treatment retention	Usual care (720)–preparation/implementation (480)	9 weeks–12 weeks	94%

Monte Carlo simulation multilevel power analyses featuring clustering in opioid treatment programs (anticipated ICC: 15%) and/or counselors (anticipated ICC: 10%)

^a^Assessed among patients nested in counselors and opioid treatment programs

^b^Asssessed among counselors nested in opioid treatment programs

Aim 1 hypotheses (effect of SSL on CM Reach and CM Adoption) will be tested by examining the effect of treatment condition at a given center at a given time point, for patients nested in counselors in centers (3-level model). Generalized linear mixed models will be used to evaluate treatment effects on rates of CM Reach, Adoption, and Maintenance.

For Aim 2 analyses, generalized MSEM models will be used to model the effect of SSL implementation. Using data from prior CM trials, we assume a rate increase for Stimulant Abstinence from 25 to 40% following SSL receipt, and a treatment retention increase of 30% from 9 to 12 weeks following SSL.

For Exploratory Aim 3 analyses, MSEM models will be used to assess whether putative provider-level mediators that will be assessed via the provider surveys (e.g., implementation climate, implementation leadership, CM perceptions) are associated with change in implementation outcomes. Exploratory outcome analyses will measure putative mediators as latent factors combining measures of SSL fidelity, inner setting factors, and provider characteristics, to assess the extent to which latent factors serve as mechanisms of action for the main effect of the SSL on implementation outcomes using bootstrapped confidence intervals.

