As shown in Fig. 1, 10 OTPs crossover from implementation as usual to the SSL strategy across four discrete wedges or cohorts. At the start of each wedge, 2–3 OTPs are randomly assigned to crossover. Within each cohort, we apply the Exploration, Preparation, Implementation, Sustainment [31] process model to divide implementation activities into discrete implementation phases. Exploration activities were completed by our team in prior work designing this study [18]: the SSL strategy condition will therefore contain only Preparation, Implementation, and Sustainment activities.

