#### Organization-level: OTPs

We will recruit 10 OTPs in New England serving a mix of urban, rural, and suburban communities, with patients from a broad array of socio-economic and racial/ethnic backgrounds. Eligible OTPs must meet the following criteria: (a) prescribe FDA-approved medication to treat patients with an opioid use disorder and concurrent stimulant use; (b) enroll at least 5 new patients per month; and (c) have at least 3 counselors who offer psychosocial support to OTP patients. We estimate that approximately 8 patients will be observed via electronic medical record (EMR) pulls per month at each OTP. Across 10 OTPs and 30 months of observation, this results in an estimated 2400 EMR pulls, across 70 counselors (assuming counselor turnover).

Research staff will recruit OTPs via established relationships with Departments of Health throughout New England. The Departments of Health host regular meetings with OTPs throughout their state and the research team will be invited to present a study overview at one of these meetings. The study overview consists of a standard set of presentation slides and a visual flyer that summarizes benefits of participation. The research team used this approach to efficiently recruit 28 OTPs in their prior cluster randomized trial.

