#### Provider turnover plan

Throughout each stage of the SSL, we anticipate that a substantial proportion of counselors and leaders who consent will leave their OTP or the field entirely, and that new providers will come on board. Provider turnover research [42–44] estimates an annual turnover rate of approximately 30% among substance use disorder front-line counselors and 20% among OTP leadership. Our more recent experiences with OTPs recorded comparable rates: 32% of counselors turned over within our 6-month active implementation phase.

To address turnover, a key focus of the SSL strategy is on building the capacity of OTP leadership to provide ongoing support. We video- or audio-record SSL training and facilitation activities so leaders have easily transferrable, low-cost training materials, consistent with usual practices at the New England ATTC. Recommended training of replacement providers will consist of watching and/or listening to recordings of SSL activities. Most critically, CM providers will be required to conduct a role play that meets the CM Competence Scale benchmark before being approved to implement CM. Any time a role play is submitted by a replacement provider, a site leader will be encouraged to review it and submit their own CM Competence Scale rating. This will provide ongoing opportunities for leaders to gain practice rating CM sessions for fidelity and to compare ratings to those given by research staff.

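### The stated clustering is constant over time and has no OTP-by-wedge component, so patient-outcome tests near a 25% rate would reject too often if OTPs vary from wedge to wedge

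*Protocol article*

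**What the plan says.** The design has "10 OTPs crossover from implementation as usual to the SSL strategy across four discrete wedges or cohorts". Data are extracted at months 0, 6, 12, 18, 24 and 30, which gives five six-month periods. Eligible patients started MOUD within the past 30 days, so each period supplies mostly new patients. The protocol expects that "approximately 8 patients will be observed via electronic medical record (EMR) pulls per month at each OTP", and "this results in an estimated 2400 EMR pulls, across 70 counselors (assuming counselor turnover").

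On clustering, the Data analysis section says that the Monte Carlo power analysis models "outcome variance nested in OTPs (anticipated ICC: 15%) and/or counselors (anticipated ICC: 10"%. The note under Table 2 repeats these two ICCs for the whole table, including the abstinence and retention rows. Aim 1 is tested through the effect of condition at a given center and time point, "for patients nested in counselors in centers (3-level model"). Aim 2 is described more loosely: "For Aim 2 analyses, generalized MSEM models will be used to model the effect of SSL implementation".

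The same section adds a check on heterogeneity: "we will examine whether significant variance in treatment effects occurs at counselor- or OTP-levels", before the effect is treated as fixed at the patient level.

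No OTP-by-wedge effect, second (between-period) ICC or decay of correlation over time is mentioned.

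**The concern.** With only OTP and counselor intercepts, the OTP part of the correlation is the same for two patients admitted in one wedge as for two admitted 24 months apart. Sharing a counselor adds some extra within-wedge likeness when counselors turn over, but nothing represents an OTP having a good or bad half-year.

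That is the level at which condition is switched on. If an OTP's outcome rate moves for reasons of its own in one wedge, about 48 patients share the movement, and the model treats it as 48 independent deviations. A fixed wedge effect removes only what all ten OTPs share. The standard error for usual care against preparation/implementation is then too small, and p-values and intervals overstate the evidence. The power simulation rests on the same constant correlation.

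**Working it through.** **Inputs from the protocol.** 10 OTPs; 8 patients per month × 6 = 48 per OTP-wedge; 10 × 5 × 48 = 2400. The phase counts 720, 480 and 1200 are 15, 10 and 25 OTP-wedges of 48. ICCs are 15% (OTP) and 10% (counselor). Abstinence is 25% v 40%, Reach 2% v 22%, α = 0.05 (two-sided assumed).

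**Assumptions.** The share *s* of OTP variance that is OTP-by-wedge is not in the documents, so 0–50% is shown. Fixed wedge effects are included throughout, which favours the plan, since the article does not state them.

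**The plan's own figure (abstinence power 90%).** It was not reproduced within 2 points:
- 720 v 480 with no clustering: 99.98%.
- Counselor design effect 1 + (1200/70 − 1) × 0.10 = 2.61: 92.3%.
- OTP design effect 1 + (120 − 1) × 0.15 = 18.85: 24.7%.
- Stepped-wedge logistic mixed model with a constant OTP effect: 98.7% (z), 97.0% (t with 8 df).

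Retention has no stated SD and cannot be checked.

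**Hand calculation of the mechanism.** The variance of an OTP-wedge's log-odds around its constant level is understated by about I = 1 + n·p(1−p)·s·τ². On the latent scale with an OTP effect only, τ² = (0.15/0.85) × π²/3 = 0.581. The z-test error is about 2[1 − Φ(1.96/√I)].
- p = 25%, s = 10%: I = 1 + 9.0 × 0.058 = 1.52, error 11%.
- p = 25%, s = 20%: I = 1 + 9.0 × 0.116 = 2.05, error 17%.
- p = 2%, s = 20%: I = 1 + 0.94 × 0.116 = 1.11, error 6%.

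At 2% an OTP-wedge holds about one event (48 × 0.02), so patient noise dominates and little is lost.

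**Simulations of the constant-effect model, no treatment effect, nominal 5%.** A: logistic, OTP and 4 fixed counselors per OTP, cohorts 2/3/3/2, 600 runs. B: logistic, OTP only, cohorts 2/2/3/3, 400 runs. C: linear, OTP and counselor, with turnover to 7 counselors per OTP, 400 runs. A and B use a 25% rate. The Monte Carlo SE is about 1 point at 5%.

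| Share *s* | A (z) | B (z / t8) | C (z / t8) |
|---|---|---|---|
| 0 | 5.5% | 5.3 / 1.8% | 2.8 / 1.3% |
| 5% | – | 9.3 / 4.8% | 11.5 / 6.0% |
| 10% | 9.2% | 12.0 / 7.3% | 17.2 / 9.2% |
| 20% | 14.0% | 17.0 / 12.8% | 25.8 / 16.8% |
| 50% | 26.2% | 29.5 / 23.5% | 41.0 / 32.8% |

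In C at *s* = 20% the model's SE is 0.071 and the true SE 0.120. Then 1.96 × 0.071/0.120 = 1.16, an error of about 25%, which agrees with the simulated 25.8%.

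**Reach under A.** At a 2% rate: 2.7, 5.7, 5.7 and 8.0% for *s* = 0, 10, 20 and 50%. At a 10% rate, which is not a planned Reach value: 5.2, 7.5, 10.5 and 19.7%.

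**With an OTP-by-wedge intercept (z test).** A at 25%: 6.3, 6.5 and 6.7% for *s* = 10, 20 and 50%. C: 7.0, 6.8 and 5.5%; with t8 about 3%.

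**Power with that intercept, abstinence 25% v 40%.** A gives 92.5% at *s* = 20% and 78.2% at 50%. The linear approximation is Φ(d/SE − 1.96) with d = 0.15/√(0.325 × 0.675) = 0.320. With SE = 0.089, 0.100, 0.120 and 0.161 it gives 95, 89, 76 and 51% for *s* = 5, 10, 20 and 50%.

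**The case against.** **Aim 2.** The largest harm falls on abstinence, for which the article says only that generalized MSEM will be used. The 3-level model is written for Aim 1, and a full analysis plan may specify more. This stands as a limit: carrying the structure over to Aim 2 is an inference from the Table 2 note.

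**Primary aim.** A reader might infer that the primary Reach test is compromised. On the planned 2% it is barely affected.

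**The heterogeneity check.** An OTP-level random SSL effect, if always kept, brings the error in the linear model down to 6.7% at a 10% share and 9.0% at 20% (z), or 3.3% and 5.7% (t8). That is a real mitigation. But the check concerns variation in the treatment effect, is conditional on significant variance, and does not represent wedge-to-wedge variation in an OTP's outcome level.

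**Evidence for movement.** A reader might take the remark that "32% of counselors turned over within our 6-month active implementation phase", or the account of shifting state policy, as the protocol describing OTPs that drift between wedges. It does not go that far. The turnover figure comes from the team's experience with other OTPs, and a counselor intercept absorbs part of it. The policy changes are national or state-level and fell between proposal and funding. The text makes OTP-specific movement plausible but does not state it.

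**Limits of the simulations.** One binary outcome per patient was used, whereas Table 1 defines abstinence over urine screens. Retention was not simulated. The article does not fix a z test.

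**Conclusion.** The point holds conditionally. The clustering that the article states is constant over time, while condition varies by OTP and wedge. With wedge effects in the model, an OTP-by-wedge share of 10–20% raises the nominal 5% error for an outcome near 25% to roughly 9–26% with a z test. With t on 8 df the figures are about 7–17%. At a zero share there is no inflation, and at the planned usual-care Reach of 2% there is little.

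It would be tempting to conclude that the 90% abstinence power is overstated. The calculations do not show that. Power with the added term is above or near 90% for small shares. At 20% the two calculations disagree (92.5% and 76%), and at 50% both fall below 90%. The figure holds only for small to moderate shares.

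**What to change.** Add a random OTP-by-wedge intercept to the Reach model and to the abstinence and retention models, next to the OTP and counselor intercepts. Keep it whether or not its variance is significant, because ten OTPs give little power to detect it. State a small-sample reference distribution suited to ten OTPs. State the Aim 2 random-effect structure explicitly.

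Rerun the Table 2 simulation with the OTP-by-wedge share set to, for example, 0, 10, 20 and 50%, and report Aim 2 power as a range.

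The cost is one more variance component, somewhat wider intervals, a rerun of an existing simulation, and possibly a less favourable stated power. No extra data are needed, and the Trial status section says that no organization or provider had been enrolled, so the change could be prespecified.

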**Fig. 1 Fig1:**
[figure not shown]
Stepped wedge design and timeline. Ten opioid treatment programs are randomized to crossover from usual care (depicted in grey) to receipt of the Science to Service Laboratory across four wedges. The Science to Service Laboratory consists of preparation activities (depicted in blue) and active implementation activities (depicted in yellow). Following 6 months of active Science to Service Laboratory support, the programs shift into a sustainment phase (depicted in green) during which they receive minimal support. Programs provide data at the 0, 6, 12-, 18-, 24-, and 30-month marks

During the first wedge, two OTPs will be randomly selected to crossover from usual care into the SSL implementation strategy condition. These two OTPs receive the SSL elements corresponding to the Preparation and Implementation phases of implementation. During the second wedge, the next cohort of two OTPs receives the SSL elements corresponding with the Preparation and Implementation phases and the first cohort shifts to the Sustainment phase, during which SSL activities are stopped and sustainment is tracked. The crossover pattern continues until all OTPs have received active SSL support. Randomization will be done using a random number generator prior to the start of each wedge by the study statistician. Immediately after randomization, he will inform the study team, who will commence scheduling of Preparation activities with the randomly selected sites. To ensure decoupling of financial support with the randomization to the SSL, OTPs receive a flat stipend each year that they participate in the study.

A key benefit of the stepped wedge trial is the extended timeline to measure sustainment. Over a 30-month study, the stepped wedge design allows the first wedge to provide sustainment data for up to 24 months.

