We ultimately made two changes to ensure the stepped-wedge trial would be acceptable to our partners. First, we substantially condensed the study timeline so that the longest an OTP would need to wait for intensive support would be 2 years. We had initially proposed a stepped wedge trial spanning 60 months (a timeline considered acceptable by our partners when we wrote the protocol, but far too slow once the protocol was funded), and we refined our timeline to 30 months. Second, we agreed to provide all OTPs participating in the study a 1-h self-paced webinar on CM immediately after the study start-up phase, to satisfy SAMHSA grant requirements and address the needs of our Department of Health partners. When we wrote the initial proposal, we presumed that OTPs would not have received any CM training; we now more realistically expect OTPs to have received basic CM education, as expected by SAMHSA and other state funders. This design will enable us to evaluate whether the full SSL strategy is superior to real-world implementation as usual, since CM webinars and brief training encounters are becoming more commonplace. In our experience working with the New England ATTC, organizations are highly unlikely to successfully implement a behavioral intervention like CM after a brief training encounter (please see our recent commentary, in which we noted the insufficiency of “one shot training” for greater discussion of this issue [15]); therefore, we do not expect the provision of this webinar to have any notable effect on our power assumptions or sample size calculations.

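### Table 2 counts all 70 counselors in both Adoption conditions, which turnover and the implied roll-out rule out, and the 720/1200 patient split does not match the two-then-two cohorts in the text

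*Protocol article*

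**What the plan says.** All references are to the protocol article.

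- **Counselors.** Under Organization-level: OTPs, 10 programs are followed for 30 months at about 8 patients per month each, and "this results in an estimated 2400 EMR pulls, across 70 counselors (assuming counselor turnover"). In Table 2 (Data analysis) the Adoption comparison is "Usual care (70)–preparation/implementation (70"), with predicted rates of 10% and 50% and a stated power of 95%.
- **Patients.** The first sentence of Data analysis splits the 2400 record pulls into 720 in usual care, 480 in preparation/implementation and 1200 in sustainment. Table 2 uses the same numbers.
- **Roll-out.** Study design allows two or three programs per wedge over four wedges. The text after Fig. 1 then puts two programs in the first wedge and continues: "During the second wedge, the next cohort of two OTPs receives the SSL elements". Active support lasts six months (2 preparation, 4 implementation). The same section says that "the stepped wedge design allows the first wedge to provide sustainment data for up to 24 months" in a 30-month study.
- **Wait.** The Discussion says that the timeline was condensed so that "the longest an OTP would need to wait for intensive support would be 2 years".
- **Turnover.** The Provider turnover plan cites about 30% a year for counselors and, from recent experience, that "32% of counselors turned over within our 6-month active implementation phase".

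**The concern.** If 70 is everyone who works as a counselor at any time in the study, it cannot also be the number observed in usual care and, again, the number observed under support. A counselor who stays through the crossover properly counts in both conditions. One hired afterwards, or one who leaves before it, counts in only one. The first cohort adds to the shortfall if it crosses over at month 0.

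The patient numbers raise a related but smaller question, namely which roll-out they were computed from, because the cohort sizes in the text do not produce them.

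At stake are a stated input to the Adoption power and the reader's ability to reconstruct the schedule that fixes how much usual-care and sustainment data each cohort gives.

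**Working it through.** **1. Reproduce the patient split.** Expected pulls in a phase = 8 × Σ(cohort size × months in that phase). Up to 24 months of sustainment in 30 months, after 6 months of active support, puts the first crossover at month 0 (30 − 6 − 24 = 0). Six-month wedges then start at months 0, 6, 12 and 18.

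- Support, any order: 10 × 6 = 60 program-months, × 8 = 480. Reproduced.
- 2-3-3-2, usual care: 3×6 + 3×12 + 2×18 = 90, × 8 = 720. Sustainment: 2×24 + 3×18 + 3×12 + 2×6 = 150, × 8 = 1200. Reproduced.
- 3-2-2-3, usual care: 2×6 + 2×12 + 3×18 = 90; sustainment: 3×24 + 2×18 + 2×12 + 3×6 = 150. Also reproduced.
- No other order of four cohorts of two or three that sum to ten gives 720/1200.

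**2. Apply the roll-out in the text.** Two programs, then two, leaves six for two wedges of at most three, so 2-2-3-3. Usual care: 2×6 + 3×12 + 3×18 = 102, × 8 = 816. Sustainment: 2×24 + 2×18 + 3×12 + 3×6 = 138, × 8 = 1104. Usual care is 13% above the stated figure and sustainment 8% below. In design-effect approximations for Reach and Stimulant Abstinence, moving from 720 to 816 changed power by less than half a percentage point.

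**3. Longest wait.** With starts at 0, 6, 12 and 18, the last cohort waits 18 months.

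**4. Counselors if 70 means posts.** Seven per program. Only programs with usual-care months count: 8 × 7 = 56 if the first cohort is two, 7 × 7 = 49 if it is three. Support: 10 × 7 = 70.

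**5. Counselors if 70 means everyone ever employed.** Assume constant staffing and immediate replacement at rate r per period over k periods, so that the number in post is N = 70/(1 + rk).

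- 30% a year: N = 70/(1 + 0.30×2.5) = 40, or 4 per program. Support: 40 × 1.15 = 46. Usual care, 2-3-3-2: 3×4×1.15 + 3×4×1.30 + 2×4×1.45 = 41. For 3-2-2-3: 2×4×1.15 + 2×4×1.30 + 3×4×1.45 = 37.
- 32% per six months: N = 70/(1 + 0.32×5) = 26.9, or 2.69 per program. Support: 26.9 × 1.32 = 35.5. Usual care: 34.5 (2-3-3-2) or 31.8 (3-2-2-3).

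**6. Effect on Adoption power.** Rates 10% and 50%, two-sided 0.05, ICC 15%, design effect 1 + (m − 1)×0.15 with m counselors per contributing program in that condition, effective n = n / design effect. Two normal approximations: the null standard error unpooled, or pooled (stricter).

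| Usual care / support | Design effects | Unpooled | Pooled |
|---|---|---|---|
| 70 / 70 | 1.90, 1.90 | 98.6% | 97.6% |
| 56 / 70 | 1.90, 1.90 | 98.1% | 96.0% |
| 49 / 70 | 1.90, 1.90 | 97.6% | 94.5% |
| 41 / 46 | 1.62, 1.54 | 95.6% | 92.0% |
| 37 / 46 | 1.64, 1.54 | 94.9% | 90.1% |
| 34.5 / 35.5 | 1.50, 1.38 | 92.9% | 88.4% |
| 31.8 / 35.5 | 1.53, 1.38 | 92.1% | 86.3% |

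Neither formula returns the stated 95% at 70/70, because the simulation settings are not given. The change down each column is more informative than the level. A small cluster-level simulation with four counselors per program, eight programs in usual care and ten in support, analysed by a paired test on the eight with both, gave 91%.

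**The case against.** **The patient split is achievable.** A reader might infer that 720/480/1200 cannot come from this design. That goes too far: two cohort orders give it exactly, and both respect the two-or-three rule and the 24 months of sustainment. The clash is only with the size given for the second cohort. This objection stands.

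**Counselors cross over with their program.** Being in both conditions is what a stepped wedge intends. This too stands; the error is counting all 70 in both.

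**70/70 might mean posts, with the month-0 data pull as usual care for every program.** The article does not say so. Table 1 times Adoption at the end of each wedge, the 720 gives the first cohort no usual-care patients, and the recruitment section describes 70 as a total that allows for turnover.

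**The two-year wait.** A reader might infer a first crossover at month 6 (1296/480/624 under 2-2-3-3), leaving the last cohort without sustainment data. The documents do not support this. Two years is a stated maximum, its starting point is undefined, and the 24 months of sustainment excludes that schedule. The schedule behind 720/1200 leaves the last cohort six months of sustainment.

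**Power might seem to collapse.** Scaling the standard error behind the stated 95% to 41/46 or 34.5/35.5 would give about 82% or 72%. That holds the clustering inflation fixed although fewer counselors per program reduce it, so those figures should not be used.

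**Conclusion.** The point holds in a limited form. With any turnover, a study-wide total of 70 cannot fill both Adoption cells, whatever the schedule. Under the schedule implied by the patient numbers, usual care holds 49 to 56 counselors on the generous reading. On the reading that the recruitment section suggests, it holds about 32 to 41, against 36 to 46 under support. The second set rests on assumed turnover, constant staffing and immediate replacement, so it shows a range and is not a prescription.

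The stated n is wrong as written. The loss of power is probably modest: about 92 to 98% unpooled or 86 to 96% pooled, with the design effect matched to cluster size. It could be larger under a harsher variance model, which the article does not specify.

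The mismatch between the text's two-then-two cohorts and 720/1200 is real, with little consequence for patient-level power. The two-year wait is a minor point of clarity. Fig. 1 is not available here, so nothing is claimed about what it shows.

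**What to change.** - State one schedule: the month of first crossover and the number of programs in each wedge. Bring Study design, Data analysis and Table 2 into line with it, and check Fig. 1 against it.
- Restate the expected patients per condition from that schedule.
- Say whether 70 counselors means posts or everyone ever employed, and give the number expected to be observable in each condition. Rerun the Adoption simulation with those numbers and restate n and power in Table 2.
- In the Discussion, say from when the two-year maximum wait is counted, or give the wait that the schedule implies.

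The cost is text and table corrections and one simulation rerun. The article reports no enrolment yet, so no data are affected. The Adoption n, and possibly its power, will look less favourable.

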The SSL has demonstrated effectiveness in promoting the implementation of CM targeting attendance [20], but has never been evaluated for the implementation of CM targeting stimulant use. Furthermore, prior SSL studies have been subject to several limitations. First, previous investigations have confounded receipt of the SSL implementation strategy with provision of CM resources by providing OTPs a fully stocked prize cabinet at the start of implementation [20, 21, 24]. Second, SSL trials have only measured sustainment for up to 6 months [24], which limits conclusions about the ability of OTPs to continue CM implementation without active support. Finally, studies of the SSL have not rigorously tracked adherence to implementation strategy [20, 21, 24]. The current project will address these three gaps by: decoupling the SSL strategy from the provision of incentives; using a stepped wedge design that enables monitoring of sustainment over a longer time horizon; and rigorously specifying and tracking the SSL strategy.

Our protocol is guided by three specific aims:Specific aim 1 (primary aim): to test the effectiveness of the SSL on implementation outcomes. It is hypothesized that receipt of the SSL will be associated with significant increases in: CM Reach (percent of patients receiving CM), CM Adoption (percent of providers delivering CM), and CM Maintenance (reach and adoption after removal of active support).Specific aim 2 (secondary aim): to test the effectiveness of the SSL on patient outcomes. It is hypothesized that receipt of the SSL will be associated with significant increases in: Stimulant Abstinence (percent of stimulant-negative screens) and Treatment Retention (number of treatment sessions).Specific aim 3 (exploratory aim): to evaluate contextual determinants, including SSL adherence, as putative mediators of implementation outcomes. It is hypothesized that contextual factors at the organization-level (e.g., implementation climate, leadership) and provider-level (e.g., perceptions of CM) will partially explain the effect of the SSL on implementation (Aim 1) outcomes.

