#### Preparation phase

Each wedge begins with 2 months of Preparation activities. At the start of this phase, counselors and leaders will complete the first of three provider surveys and a team-based inventory.

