#### Implementation phase

When preparation activities are complete, OTPs shift into the active Implementation phase lasting 4 months. The goal of this phase is to commence CM implementation and integrate it into the usual workflow.

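### The only stated Maintenance comparison sets Sustainment against an earlier SSL phase, so it cannot test the hypothesised SSL-caused increase, and pooling Preparation months can mask part of a post-support decline in Reach

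*Protocol article*

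**What the plan says.** The specific aims at the end of the Background give one directional hypothesis for all three primary-aim outcomes. It opens "It is hypothesized that receipt of the SSL will be associated with significant increases in: CM Reach (percent of patients receiving CM" and closes its list with "CM Maintenance (reach and adoption after removal of active support". The predicted increase is attributed to receipt of the SSL.

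Table 2 (Data analysis) then names the comparison for each outcome. Reach has "Usual care (720)–preparation/implementation (480". Adoption and both Aim 2 outcomes also have usual care on one side. Maintenance alone has "Preparation/implementation (480)–sustainment (1200", with usual care on neither side.

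The phase called Preparation/Implementation has two parts. The Preparation phase section says "Each wedge begins with 2 months of Preparation activities". The Implementation phase section describes the next 4 months, and says of them "The goal of this phase is to commence CM implementation and integrate it into the usual workflow".

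The text after Table 2 says that generalized linear mixed models will evaluate treatment effects on Reach, Adoption and Maintenance. It names no contrast for Maintenance.

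**The concern.** An effect of receiving the SSL needs a reference that has not received it. In this design that is usual care. A contrast between Sustainment and the preceding active phase answers a different question: how far delivery moves once support stops. The two can point in opposite directions, so a program that supports the hypothesis can look like a failure in the stated comparison.

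The stated comparison is also imperfect for its own question. One third of the comparator's months precede the phase in which CM delivery begins. If Reach is low among patients admitted in those months, the reference is lowered, and some of a true loss after support ends will not show.

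Maintenance belongs to the primary aim, and short follow-up of sustainment is one of three gaps in earlier SSL work that the Background says this trial will close.

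**Working it through.** **Inputs.** 10 OTPs, 30 months, and "approximately 8 patients will be observed via electronic medical record (EMR) pulls per month at each OTP" (Organization-level: OTPs). Four wedges of 2–3 OTPs; the first wedge gives up to 24 months of sustainment data (Study design), so crossovers fall at months 0, 6, 12 and 18. Preparation 2 months, Implementation 4 months. Reach 2% in usual care and 22% in pooled Preparation/Implementation, α = 0.05 (two-sided assumed), ICC 15% for OTPs and 10% for counselors (Table 2).

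**1. Reproducing the counts.** The plan says "Across 2400 EMR pulls, 720, 480, and 1200 are expected to occur during Usual Care, Preparation/Implementation, and Sustainment phases, respectively". With 2.5 OTPs per wedge on average:
- Usual care: 2.5 × (0 + 6 + 12 + 18) × 8 = 720
- Preparation/Implementation: 10 × 6 × 8 = 480
- Sustainment: 2.5 × (24 + 18 + 12 + 6) × 8 = 1200

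All three agree. They are exact for wedge sizes 2/3/3/2 or 3/2/2/3. Sizes 2/2/3/3 would give 816/480/1104; the 480 does not change.

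**2. What each contrast shows.** Take a sustained Reach of 11% (illustrative, half of 22%).
- Sustainment v usual care: 11% − 2% = +9 points, an increase as hypothesised.
- Sustainment v Preparation/Implementation: 11% − 22% = −11 points, a decrease.

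On independent observations (720 v 1200 and 480 v 1200), each difference has power above 99%. These are upper bounds, since clustering and calendar time are ignored.

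**3. Dilution of the comparator.** Preparation contributes 10 × 2 × 8 = 160 records and Implementation 10 × 4 × 8 = 320. Pooled Reach = (2 × prep + 4 × impl)/6, so with pooled Reach at 22%, impl = (6 × 22% − 2 × prep)/4.

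| Preparation-month Reach (assumed) | Implementation-month Reach | Decline masked, points | Decline masked, relative |
|---|---|---|---|
| 2% | 32% | 10 | 10/32 = 31% |
| 10% | 28% | 6 | 6/28 = 21% |
| 22% | 22% | 0 | 0% |

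**4. Behaviour of the test in the first row.**
- True fall from 32% to 22%: the pooled contrast sees 22% v 22% and rejects at about 5%, which is α alone. Against the Implementation months only (320 v 1200), power is about 95% on independent observations. It is about 90% in a simple 10-OTP simulation with the stated ICCs and a paired t-test.
- No fall, 32% sustained: the pooled contrast shows a spurious rise of 10 points (power about 99%, independent observations).

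**5. Calendar time.** Usual care ends at month 18. Before then, Sustainment covers 12 months in wedge 1 and 6 in wedge 2: 18 × 2.5 × 8 = 360 of 1200 records, or 30%. For sizes 2/3/3/2 this is (2 × 12 + 3 × 6) × 8 = 336; for 3/2/2/3 it is (3 × 12 + 2 × 6) × 8 = 384. Sustainment overlaps the active phase in months 6–24: (18 + 12 + 6) × 2.5 × 8 = 720 records. Mean calendar month is (3 + 9 + 15 + 21)/4 = 12 for active data and (24 × 18 + 18 × 21 + 12 × 24 + 6 × 27)/60 = 21 for Sustainment, 9 months later.

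**6. Cost of removing Preparation elsewhere.** For abstinence at 90% power, the detectable signal is 1.96 + 1.28 = 3.24 standard errors. Using 320 records instead of 480 multiplies it by √[(1/720 + 1/480)/(1/720 + 1/320)] = 0.877, giving 2.84. Power is then Φ(2.84 − 1.96), about 81%, if the effect is unchanged and the standard error scales with record counts.

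**The case against.** Table 2 reports power simulations; it is not the analysis specification. The text on the mixed models leaves the Maintenance contrast open, and an analysis plan not shown here may name usual care as the reference. This stands as a limit on the claim. A reader might infer that benefit over usual care will not be tested at all; the document does not go that far. What it does is state one comparison, and that one does not match the hypothesis.

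A reader might also infer that the pooling does hide a decline. That is only the worst case:
- Reach counts any patient with at least one CM encounter, sets no window for the first encounter, and is measured at wedge end (Table 1). Patients admitted in Preparation can count once CM starts, and the dilution could be nil.
- Adoption counts counselors with at least one encounter, also at wedge end, so Preparation months do not dilute it in the same way.
- Large declines remain visible.
- The 22% in Table 2 is the prediction for the pooled phase. Treating it as the Implementation-month rate would misread the table.

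Nothing in the text says that a non-significant difference would be read as successful maintenance, and no such intention should be attributed to the investigators. No weight is placed on the empty rate and power cells in the Maintenance row, which may have been lost when the table was extracted.

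Finally, the SSL condition is defined to include Preparation, and exposure begins at the randomised crossover. Keeping Preparation there is defensible; for Reach against usual care, any dilution is conservative.

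**Conclusion.** The mismatch holds. The hypothesis is an SSL-caused increase, and the only stated Maintenance comparison has the SSL on both sides. That conclusion needs no numerical assumption; the 11% example only shows that the two contrasts can disagree in sign.

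The pooling is a secondary and conditional defect. It rests on reading 22% as the pooled rate and on Preparation-month Reach, which the article does not give and which is taken here as 2% to 22%. It concerns Reach only. Its size runs from nothing to just under one third of Implementation-month Reach.

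The stronger conclusion that Preparation must be taken out of the SSL condition in every model is not supported. That would be a trade-off with a real cost in power for abstinence, not the correction of an error.

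**What to change.** 1. State that the Maintenance hypothesis is tested as Sustainment v usual care, for Reach and Adoption, in a model adjusted for calendar period. Give this contrast its own simulated power. State openly that about 70% of Sustainment records have no concurrent usual care, so the estimate depends on how period is modelled.
2. Report the change after support ends as a separate question: Sustainment v the 4 Implementation months, as a confidence interval against a margin set in advance. State that non-significance is not evidence of maintenance.
3. Bring the Maintenance row of Table 2 and the text on the mixed models into line with items 1 and 2.
4. Keep Preparation within the SSL condition for the Reach and Aim 2 contrasts against usual care. Separating it there is optional, and power would have to be re-simulated.

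The cost is mainly wording and one further power simulation. Item 2 uses 320 reference records instead of 480, and assumes that the extract lets each patient's admission be assigned to Preparation or Implementation. The Trial status section says that no organisation had been enrolled when the article was written; if the trial has since moved on, the change should be fixed before outcome data are compared by phase.
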